## Summary

The following study is a pilot study for a subsequent, large RCT to prove the efficacy of acupuncture in persons with increased stress levels. The explorative study is designed as three-arm study with a partially standardized verum acupuncture treatment according to Traditional Chinese Medicine (TCM), a sham acupuncture treatment, as well as a waiting control group. Before the beginning and after the conclusion of the treatment, clinical and psycho-neuro-immunological parameters, together with heart rate variability are examined in order to estimate the magnitude of the effects of acupuncture. In addition, the pilot study investigates the feasibility of the design itself.

## 1 Introduction

The term „stress“ is an often-used concept in our daily life. But stress is understood differently by people and is associated with factors of life such as overwork, noise, financial worries, etc.

Generally, one can define stress as a threat of inner equilibrium through internal and external threats, so-called stressors. Hans Selye, father of stress research, defined stress as the non-specific reaction of an organism to various demands (Selye, 1956). In fact, stress is a normal reaction of the body and helps us to adapt to various situations. When a person is confronted by a demanding situation, the body reacts by temporarily reducing all body functions in order to quickly react to the problem, with the help of our reflexes.

Once the situation is successfully dealt with, a recovery phase emerges. Problems arise when the situation cannot be dealt with successfully or appropriately: a phase of exhaustion then emerges, in which the body is in a constant state of alarm, and is consequently weakened.

It is known that chronic stress is a risk factor or amplifier for various bodily complaints or diseases. Chronic stress demonstrably leads to an increase of cardiovascular risk, to increased musculoskeletal complaints, and mental disorders (e.g. depression). (Hammen *et al.*, 2009, Rosengren *et al.*, 2004). Furthermore, it has been shown that high chronic stress levels lead to a change of the immune system together with an increased frequency of infections. These developments are alarming not only for the individual patient – they also represent a major problem in the area of Public Health. Preventive measures to reduce the stress level and subsequent diseases are therefore urgently needed.

Acupuncture, a part of the Traditional Chinese Medicine (TCM), has long been used as a treatment for stress-related disorders. To date, a few studies have shown that acupuncture may serve as treatment for persons with increased stress (Huang *et al.*, 2011). However, well-designed randomized-controlled (RCT) studies demonstrating the efficacy of acupuncture in chronic stress are still lacking.

## 2 Goals of the study

The planned study (AkuReSt) is designed as an explorative pilot study with the aim of investigating the feasibility of the design itself as well as to estimate effect sizes in relation to clinical and psycho-neuro-immunological parameters.

## 2.1 Outcome parameters

### Feasibility

An outcome parameter of the pilot study is its feasibility. The study is defined as feasible when at least 70% of the included patients complete the study. In addition, the recruitment rate, the acceptance of the randomization, and the adherence to the intervention will be measured.

### Questionnaires and psycho-neuro-immunological measurements

A patient-relevant outcome measure of the pilot study is the stress reduction – measured by validated questionnaires such as the Percieved Stress Questionnaire (PSQ-20) and the stress module of the PHQ (Fliege *et al.*, 2005, Löwe *et al.*, 2001). The PSQ-20 is designed to be the primary outcome of the subsequent large RCT study. The sample size calculation of the subsequent large RCT will be based on the estimates of the PSQ-20 changes of the present pilot study.

Secondary outcome parameters, measured by questionnaires, are somatoform complaints, depression severity, general anxiety severity (PHQ), (Löwe *et al.*, 2001), quality of life (EQ-5D) (Hinz *et al.*, 2014), and the self-assessed medical outcome profile (Measure Yourself Medical Outcome Profile (MYMOP) (Hermann *et al.*, 2014).

In addition to the questionnaire measurements psycho-neuro-immunological assessments are conducted. To date, little is known regarding the psychophysiological effects of acupuncture in increased stress; various immunological stress-parameters will therefore be analyzed as markers for balance or disorders (pre-post treatment).

Further, the heartrate variability of the participants will be measured before and after the treatment (or waiting period).

## 2.2 Hypotheses

The following hypotheses will be investigated in the framework of the study:

- (1) The study design is well accepted by persons who met the inclusion criteria. The number of consenting persons is greater than 50%. In addition, more than 70% of the included persons complete the study;
- (2) Explorative: The acupuncture intervention leads to a clinically relevant reduction of the stress level (measured by the PHQ-stress module and the PSQ-20);
- (3) Explorative: Acupuncture treatment leads to a change in psycho-neuro-immunological and psychophysiological parameters;
- (4) Verum acupuncture shows a tendency for greater stress reduction compared to sham acupuncture. Significant results are to be expected in a larger RCT;
- (5) Compared to the control group sham acupuncture shows a reduction in stress levels.

### 3 Assessment procedures

In the frame of the study person-specific data are measured (sex, age, weight). The assessment also includes self-assessment of the stress level, quality of life, and somatic complaints (questionnaires) as well as the measurement of heart rate variability before and after the acupuncture treatment.

The psycho-neuro-immunological parameters are measured by using blood and urine samples.

### 4 Study design

The study is planned as an explorative randomized controlled trial. The design is prospective with three measurement time points: T0 (baseline measurement), T1 (at the end of treatment or waiting period), and T2 (follow-up after three months). The intervention condition (verum acupuncture) is compared to an active control condition (sham acupuncture) regarding the acupuncture treatment as well as with a waiting control group.  $N = 3 \times 25 = 75$  persons should be included and randomized to three conditions.

The intervention treatment consists of 10 acupuncture sessions (each session is from 20-30 minutes in length) and is implemented by a licensed acupuncturist (additional title “acupuncturist” or equal amount of training sessions). Intervals between treatments should vary from 3 to 7 days. For all acupuncture sessions, sterile, single-use filiform acupuncture needles, with a length of 25 mm and a diameter of 0.25 mm each, will be used. For the verum acupuncture a semi-standardized protocol is defined according to literature research and the expertise of the acupuncturists. Three acupuncture points are fixed and maintained throughout the 10 sessions; up to four points will be individually selected by the acupuncturist (maximum 7 acupuncture points and 12 needles). The individual points can be chosen and altered during the course of treatment by the acupuncturist in accordance with the main clinical symptoms. Eliciting a De Qi sensation is the aim of the verum acupuncture treatment; after 10-15 minutes of acupuncture treatment the needles can again be stimulated by the acupuncturist.

The active control condition for the verum acupuncture is a sham acupuncture treatment. For the sham acupuncture, 4-6 standardized points of acupuncture that are not located on acupuncture meridians are chosen (i.e. non-acupuncture points). These points are needled only superficially, that is, without eliciting the so-called De Qi sensation; the control acupuncture points can be changed individually during the course of treatment similar to the verum acupuncture (maximum 12 needles).

From the outset, participants in the waiting control group will receive no acupuncture treatments over the course of three months.

## 5 Inclusion- and exclusion criteria

### Inclusion criteria:

- Age  $\geq 18$  years
- PSQ-score  $\geq 60$

(The PSQ-20 includes 20 items regarding self-perceived everyday life stress. These items can be answered on a scale ranging from 1 (“almost never”) to 4 (“most of the time”). The total score of the PSQ – which can be compared with norm values – is calculated by transforming the item scores to 0-3, and then by dividing by 3 (linear transformation to the range of 0-1). Multiplication with the factor 100 results in a total score that ranges between 0 and 100. A total score  $> 60$  is an indicator for high stress (Kocalevent et al., 2007, Levenstein et al., 1993).

### Exclusion criteria:

- Acute suicidality
- Acute psychiatric disorder
- Needle phobia
- Insufficient knowledge of the German language

## 6 Randomization procedure

The randomization will be conducted by using the program „RANDI2“ - to be stratified by the participating centers

Participants in the waiting control group will receive no acupuncture treatments over the course of three months, after which they will be offered a verum acupuncture treatment.

## 7 Course of the study

Eligible study participants will be informed about the study by advertisements. Interested persons will be included in the study if they meet the inclusion criteria and give their informed consent. A baseline measurement will be done (questionnaires, salivary and blood samples, urine samples); participants are then randomized. According to their randomization group they will receive the treatment, as described above (verum acupuncture, sham acupuncture, or waiting control group).

The second assessment (questionnaires, salivary - and blood samples, urine samples) will be done at the end of treatment or waiting time (three months). For all participants, a three-month follow-up will be conducted (questionnaires, salivary- and blood samples, urine samples).

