## **Heart rate variability**

The heart rate variability will be measured at both the beginning and end of the treatment.

With the patients in the acupuncture group, these tests will be implemented 5 minutes before the acupuncture treatment (for approx. 20 minutes) and 5 minutes after the acupuncture treatment. (In total, approx. 30 minutes.) In the control group, heart rate variability will be measured during resting time for approx. 30 minutes using the same timelines.

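### The T1 rules do not fit together: ten sessions end 27 to 63 days after the first, the waiting arm is assessed at three months, and contrasts with the waiting arm may compare unequal elapsed times

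*Protocol*

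**What the plan says.** Section 4 (Study design) defines the first post-baseline time point as "T1 (at the end of treatment or waiting period"). It sets the length of the course through two figures: "The intervention treatment consists of 10 acupuncture sessions" and "Intervals between treatments should vary from 3 to 7 days".

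Section 7 (Course of the study) says the second assessment "will be done at the end of treatment or waiting time (three months").

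Sections 4 and 6 give the length of the wait. In section 6: "Participants in the waiting control group will receive no acupuncture treatments over the course of three months". Verum is then made available to this arm, once the wait is over.

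On T2, section 7 says "For all participants, a three-month follow-up will be conducted". Neither section 4 nor section 7 says whether those three months run from T1 or from baseline.

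The heart rate variability subsection says that in the control group "heart rate variability will be measured during resting time for approx. 30 minutes using the same timelines".

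No section sets a common calendar time for T1, ties the waiting-arm T1 to the length of the needle course, or states the delay from baseline or randomisation to the first session.

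**The concern.** T1 is tied to an event in the needle arms (the end of the course) and to a fixed period in the waiting arm. The event, worked out from the protocol's own session figures, comes well before the fixed period ends. A contrast between a needle arm and the waiting arm then mixes the effect of treatment with the effect of time.

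Time matters for this outcome. Entry requires a PSQ score of at least 60, and the PSQ-20 is also the patient-relevant outcome, so some change without treatment is to be expected after selection.

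Estimating effect sizes is one of the two stated goals of the pilot (section 2), and section 2.1 bases the sample size of the later trial on the PSQ-20 changes seen here. Hypothesis 5 is explicitly sham versus the control group. If the T1 times do not overlap, arm and elapsed time are fully confounded, and adjusting for time would be extrapolation. The visit schedule can prevent this. The analysis cannot repair it afterwards.

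**Working it through.** The protocol states no treatment duration, so there is no figure of its own to reproduce. The check is calendar arithmetic.

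**Inputs**
- Sessions: 10, hence 9 intervals (section 4).
- Interval: 3 to 7 days (section 4).
- Waiting period: three months (sections 4, 6 and 7), taken as 365.25 / 4 = 91.3, about 91 days.
- Delay from randomisation to session 1: not stated; taken as short (assumption).
- Sham schedule: taken to be the same as verum. The session count and intervals are written for the intervention treatment, and their use for sham is implied only.

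**Reading A: three months applies to the waiting arm only**
- End of course, counted from session 1: 9 × 3 = 27 days to 9 × 7 = 63 days (3.9 to 9.0 weeks).
- Waiting-arm T1: about 91 days (13.0 weeks).
- Offset: 91 − 63 = 28 days to 91 − 27 = 64 days.
- Overlap: none, because the slowest permitted course ends on day 63, before day 91.
- Sensitivity: with three months taken as 84 to 92 days, the offset is 84 − 63 = 21 to 92 − 27 = 65 days.
- Delay that would close the gap: 28 days for the slowest course, 64 days for the fastest. Section 7 goes from baseline to randomisation to treatment and provides for no such delay.

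**Reading B: three months applies to all arms**
- If the course is to end at three months, the mean interval must be 91 / 9 = 10.1 days (84 / 9 = 9.3 to 92 / 9 = 10.2). This is outside 3 to 7 days.
- If the intervals are kept, T1 falls 28 to 64 days (about 4 to 9 weeks) after the last session, contrary to the T1 definition in section 4.

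**T2, if counted from T1 under reading A**
- Needle arms: 27 + 91 = 118 to 63 + 91 = 154 days.
- Waiting arm: 91 + 91 = 182 days, by which time verum has been offered there.

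**Direction of any bias under reading A**
- If untreated stress falls with time, the waiting arm has one to two extra months to fall, and the effect against waiting is understated.
- If untreated stress rises, the effect is overstated.
- The protocol gives no untreated course, so neither the sign nor the size follows from it.

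**The case against.** The strongest reply is that the words in section 7 can cover all arms. T1 would then be at three months everywhere, and no contrast would mix treatment with time. This is a possible reading, and it removes the confounding. It does not remove the conflict with the session intervals or with the end-of-treatment definition of T1.

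Second, the offset needs session 1 to follow randomisation closely, and the intervals are worded as what should happen. Both points stand, and the offset is therefore conditional.

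Third, a reader might infer that every comparison in the trial is affected. The document does not support that:
- Only hypothesis 5 names the control group. Hypotheses 2 and 3 name no comparator and are touched only where the waiting arm is used as one.
- Verum versus sham (hypothesis 4), the contrast expected to show significant results in a larger trial, has no systematic offset if both arms follow the same schedule.
- The heart rate variability wording could mean matched calendar timing, although in context it reads as timing within a visit.
- The feasibility criteria do not depend on when T1 falls.

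Fourth, a reader might infer that the acupuncture effect is inflated by some number of PSQ points. Any such number would come entirely from an assumed drift. Regression after a threshold entry need not be linear over these weeks, and a falling untreated course would work against acupuncture.

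Fifth, this is an explorative pilot without confirmatory analysis, and measuring at the end of a course is a defensible choice. That lowers the stakes. It does not justify a different elapsed time in the comparator when effect sizes are a stated goal.

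**Conclusion.** The concern holds in a conditional form. Sections 4, 6 and 7 cannot all be followed with T1 both at the end of treatment and at a common time.

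On the reading that gives the waiting arm alone three months, its T1 is about 28 to 64 days later than in the needle arms, without overlap. The sham-waiting contrast and any verum-waiting effect size then compare changes over unequal periods. This rests on prompt start of treatment after randomisation, on adherence to the 3 to 7 day intervals, and on sham following the verum schedule.

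On the other reading, the elapsed times agree but T1 is 4 to 9 weeks after the last session. The documents do not settle which reading is meant.

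The bias has no derivable size or sign in PSQ points. The matter is more than missing detail, because a stated visit rule creates the mismatch and it cannot be undone once the visits have taken place. It should be settled before recruitment.

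**What to change.** Reconcile sections 4, 6 and 7 on what T1 is, and state its time origin. Session intervals and the waiting period can stay unchanged. Either of two changes removes the systematic offset:

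1. **Common time.** Define T1 at the same time since randomisation in all three arms, with a window that allows for the delay to session 1 and the longest permitted course. As an illustration, week 10 (day 70) covers a 63-day course only if session 1 takes place within 70 − 63 = 7 days of randomisation. The cost is that a 27-day course begun at once would be assessed 70 − 27 = 43 days, about six weeks, after its last session, which may dilute an end-of-treatment effect.
2. **Matching.** Keep T1 at the end of treatment in the needle arms, and schedule the waiting-arm T1 assessments used for the contrasts at the matching elapsed time. This must include questionnaires, samples and heart rate variability; matching the questionnaires alone would leave the biological contrasts unmatched. Needle-arm T1 can vary by 63 − 27 = 36 days, so the protocol should say how the match is made. The cost is that the waiting arm's T1 visit moves earlier.

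In both cases, state whether T2 runs from T1 or from randomisation. Say also that, if T2 runs from T1, the waiting arm has been offered verum by then and is no longer an untreated comparator.

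The change needs protocol wording and visit scheduling, and no additional participants.

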## **Heart rate variability**

The heart rate variability will be measured at both the beginning and end of the treatment.

With the patients in the acupuncture group, these tests will be implemented 5 minutes before the acupuncture treatment (for approx. 20 minutes) and 5 minutes after the acupuncture treatment. (In total, approx. 30 minutes.) In the control group, heart rate variability will be measured during resting time for approx. 30 minutes using the same timelines.

## **Blood and urine samples**

For both blood samples approx. 50 ml of blood are taken (three monovettes for serum samples, two monovettes heparin blood, three monovettes EDTA-blood). For the urine analyses, morning urine is used (when possible). The blood and urine samples are taken to investigate inflammatory markers (proteins, RND) and to characterize the redox milieu in blood cells and body fluids.

Excess material will be centrifuged; aliquots will be stored immediately at  $\leq -80^{\circ}\text{C}$ . A  $-80^{\circ}\text{C}$  refrigerator with emergency cooling is provided by the department. Excess material will be stored in the frame of a biobank over the course of 10 years.

## **8 Concomitant therapy /additional treatment**

Not applicable

## **9 Risks and Safety laboratory**

The questionnaires do not pose a risk for the patients.

Following the blood sampling temporary irritations or bruises can occur.

The risk of a complication due to the acupuncture treatment is estimated – on the basis of comprehensive data - as being very low.

The following adverse effects have been described: Development of a haematoma at the injection side, local pain during and after the acupuncture treatment, local skin infections, vegetative side effects such as sweating, feelings of heat/cold, and fatigue. In rare cases, a vasovagal syncope can occur during acupuncture (White et al., 2001, Wu et al., 2015)

Safety laboratory: not applicable.

## **10 Stopping rules**

A patient may withdraw from the study at any time, at his or her own request, for any reason, specified or unspecified, and without penalty or loss of benefits to which the

patient is otherwise entitled.

Stopping rules for the entire study are unknown.

## **11 Statistical design /data analysis**

### **Sample size calculation:**

Not applicable. The planned number of participants corresponds to the sample size of a pilot study. The number of participants allows for a subgroup analysis, separated for men and women.

### **Statistical analysis:**

The study is a pilot study; therefore, a confirmatory analysis will not be done. The feasibility of the study will be described by reporting the recruitment rate, acceptance of treatment and drop-out rate respectively loss-to-follow-up rate.

Changes in further outcome parameters will be estimated with effect sizes including confidence intervals. Descriptive analyses will be conducted for the immunological and metabolic parameters. Mean differences with their confidence intervals are calculated.

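### Entry requires a high PSQ-20 score, but neither hypothesis 2 nor the input to the later trial's sample size is tied to a between-arm difference, so regression to the mean can pass as an acupuncture effect

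*Protocol*

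**What the plan says.** Four places in the Protocol bear on this.

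- **Section 5, inclusion criteria:** a PSQ score of 60 or more is required. The scale is the 20-item PSQ: "Multiplication with the factor 100 results in a total score that ranges between 0 and 100".
- **Section 2.1, questionnaires:** the PSQ-20 is a patient-relevant outcome here and the intended primary outcome of the later trial. "The sample size calculation of the subsequent large RCT will be based on the estimates of the PSQ-20 changes of the present pilot study".
- **Section 2.2:** hypothesis 2 reads "The acupuncture intervention leads to a clinically relevant reduction of the stress level", as measured by the PHQ stress module and the PSQ-20, and names no comparator. Hypothesis 4 does name one: "Verum acupuncture shows a tendency for greater stress reduction compared to sham acupuncture". Hypothesis 5 compares sham with the control group. No hypothesis compares verum with waiting, although Section 4 plans that comparison.
- **Section 11, statistical analysis:** "Changes in further outcome parameters will be estimated with effect sizes including confidence intervals". After a sentence on immunological and metabolic parameters comes "Mean differences with their confidence intervals are calculated". Neither sentence says whether the quantity is within or between arms.

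Randomisation is "to be stratified by the participating centers" (Section 6).

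**The concern.** People chosen because they score high on a fluctuating scale tend to score lower when measured again, whatever is done to them. Here the selection scale and the outcome scale are the same. A pre-post fall in the verum arm therefore mixes any acupuncture effect with regression to the mean and with the natural course over the treatment period.

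Two statements make this more than a matter of style. Hypothesis 2, as worded, would be supported by a fall in the verum arm alone. Section 2.1 then passes PSQ-20 changes, not a difference between arms, into the sample size of the next trial. Estimating effect sizes is one of the pilot's two stated aims (Section 2). If the number carried forward is a pre-post change, the next trial could be several times too small.

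**Working it through.** **The plan's own figure.** Section 4 gives N = 3 × 25 = 75 and says these "persons should be included and randomized to three conditions". The arithmetic is right. There is no power calculation to reproduce.

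**Inputs.** The cut-off of 60 is from Section 5. The protocol gives no PSQ mean, SD or retest correlation. I assume a normal source population with mean μ from 33 to 50, SD s from 17 to 20 and retest correlation r from 0.7 to 0.9, and that the entry score is the analysed baseline.

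**Formulas (no treatment effect).** Let a = (60 − μ)/s and λ = φ(a)/(1 − Φ(a)).

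- Mean at entry: μ + sλ
- Expected fall: (1 − r)sλ
- Baseline variance after the cut: V0 = s²(1 + aλ − λ²)
- Variance of change: (1 − r)²V0 + s²(1 − r²)
- Variance at T1: r²V0 + s²(1 − r²)

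**Worked case: μ = 40, s = 17, r = 0.8.**

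- a = 20/17 = 1.176; λ = 0.1997/0.1197 = 1.668
- Mean at entry = 40 + 17 × 1.668 = 68.4
- Fall = 0.2 × 17 × 1.668 = 5.67 points
- V0 = 289 × (1 + 1.962 − 2.782) = 52.0, so baseline SD = 7.21
- SD of change = √(0.04 × 52.0 + 289 × 0.36) = √106.1 = 10.30
- SD at T1 = √(0.64 × 52.0 + 289 × 0.36) = √137.3 = 11.72
- Standardised fall: 5.67/10.30 = 0.55 (SD of change), 5.67/11.72 = 0.48 (T1 SD), 5.67/7.21 = 0.79 (baseline SD)

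With s = 20 and the rest unchanged, the fall is 6.1 points: 0.50, 0.44 and 0.68 on the same three scales.

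**Range.**

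| μ | s | r | Fall (points) |
|---|---|---|---|
| 50 | 17 | 0.9 | 2.1 |
| 40 | 17 | 0.8 | 5.7 |
| 40 | 20 | 0.8 | 6.1 |
| 33 | 20 | 0.7 | 10.9 |

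**What a comparator does.** I used 4,000 simulated trials of 3 × 25 with no effect (μ = 45, s = 18, r = 0.7).

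| Estimate | Mean | SE |
|---|---|---|
| Within-arm change | −7.4 | not recorded |
| Between-arm difference in change | 0.05 | 3.73 |
| Between-arm difference at T1 | 0.04 | 4.01 |
| ANCOVA difference | 0.05 | 3.69 |

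The simulation error of each between-arm mean is about 3.73/√4000 = 0.06, so all three are zero within error. Every randomised contrast removes the fall, adjusted or not.

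**What adjustment adds.** The ANCOVA residual variance is s²(1 − r²). In the worked case this is 104.0, against 137.3 for T1 scores (24% less) and 106.1 for change scores (2% less). Across the assumed ranges the reduction is about 12 to 53% against T1 scores and 1 to 5% against change scores. The gain from adding centre cannot be sized from the document.

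**What a wrong input would cost.** Two arms, 80% power, two-sided 5%: n per arm = 2(1.96 + 0.84)²/d² = 15.7/d². Carrying forward a pre-post 0.5, which can arise with no treatment effect, gives 63 per arm. A true between-arm effect of 0.3 needs 175, and 0.2 needs 393.

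**The case against.** The strongest reply is that Section 11 does not say within-arm. A change score compared between randomised arms fits its words equally well and carries no regression-to-the-mean bias. Section 4 sets verum against sham and waiting, and hypotheses 4 and 5 are between-arm. The study is exploratory and rules out confirmatory analysis, and with a randomised waiting arm the right contrast can always be computed. This stands against claiming that the plan analyses within-arm change. It does not answer hypothesis 2, which lacks a comparator where hypotheses 4 and 5 have one, or Section 2.1, which fixes the sizing input as changes.

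Three further inferences may tempt a reader, and the document does not support them.

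- **That baseline and centre adjustment is the cure, or that an unadjusted comparison is biased by chance imbalance.** Chance imbalance adds variance, not bias over randomisations, and an unadjusted between-arm difference already removes the regression effect.
- **That the planned effect size is inflated by dividing by the baseline SD.** No standardiser is named. The apparently large 0.68 to 0.79 depends on that choice; the T1 SD or the SD of change gives 0.44 to 0.55.
- **That silence on covariates is an error.** A statistical analysis plan may exist, and model terms commonly sit there.

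Section 7 does not say whether the baseline PSQ-20 is the eligibility score. If it is a separate measurement, the fall is smaller.

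**Conclusion.** The point holds as a defect in what the protocol fixes: a hypothesis without a comparator, and a sizing input described as changes, in people selected on the outcome scale. It does not show that the effect will be estimated wrongly. That happens only on the pre-post reading, which hypothesis 2 and Section 2.1 invite and the rest of the design argues against.

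On that reading, the spurious fall is about 2 to 11 points under the assumed inputs. Around mean 40 and correlation 0.8 it is about 6 points, or a medium effect of 0.50 to 0.55 SD of change. These sizes rest on the assumed mean, SD and correlation, on normality, and on the entry score serving as baseline.

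Cancellation between arms also assumes that T1 falls at comparable times. Ten sessions at 3 to 7 day intervals span 9 × 3 = 27 to 9 × 7 = 63 days, against three months of waiting. The cancellation is therefore cleaner for verum versus sham than for contrasts with the waiting group.

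The sponsor should act on this, but the pilot remains valid without it because the needed data are collected anyway.

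**What to change.** 1. **Section 2.2:** reword hypothesis 2 so that the reduction is compared with the waiting group.
2. **Sections 2.1 and 11:** state that the effect for hypotheses 2, 4 and 5, and the input to the later trial's sample size, is the between-arm difference in PSQ-20 at T1. Report verum minus sham, verum minus waiting and sham minus waiting, each with a 95% confidence interval in PSQ points.
3. **Section 11:** present within-arm changes as description only.
4. **Preferably, there or in the statistical analysis plan:** estimate the differences by ANCOVA with arm, baseline PSQ-20 and centre, for precision.
5. **If a standardised effect is reported:** name the SD used, and avoid the baseline SD, which the entry cut-off truncates.

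The cost is a few sentences and one regression model. Arm, centre and PSQ-20 at both times are already recorded; no extra participants or visits are needed.
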